### Objectives

The primary objective of this trial is to determine whether preemptive incisional infiltration with ropivacaine plus D-PAL is superior to ropivacaine alone in relieving postoperative pain for adults undergoing neurosurgical craniotomy. The effects of both interventions on postoperative pain management and patients’ safety and quality of recovery will also be compared.

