### Sample size

Earlier studies have reported that incision-site infiltration with ropivacaine plus dexamethasone could reduce about 30-50% of postoperative pain severity compared with ropivacaine alone [6, 19, 22]. Based on these literatures and our clinical experience, we hypothesize that the pain NRS scores was approximately 2.0 ± 1.5 (mean ± standard deviation) scores in the ropivacaine alone group and attempt to detect a difference of 40% in pain NRS scores between groups at 24 h after craniotomy. Therefore, the pain scores would be about 1.2 ± 0.9 scores in D-PAL plus ropivacaine group at 24 h after craniotomy. PASS V.11 software (NCSS, Kaysville, UT, USA) is used for sample size calculation with *α* = 0.05, *β* = 0.1, and power = 90%. Considering a dropout rate of 20%, a total of 130 patients will be required in this trial (*n* = 65 per group).

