## Statistics

All statistical analyses will be performed by a statistician who is blinded to the entire study. All analyses will include the patients completing 3 months of follow-up and will follow the intention-to-treat principle. Data analysis will be performed using SPSS 26.0 (SPSS Inc., Chicago, IL, USA). Kolmogorov-Smirnov test will be used to check for normal distribution. Normally distributed continuous variables will be described as mean ± SD and abnormally distributed variables as median (interquartile ranges, IQRs). Categorical variables will be reported as the number or proportion of patients. The primary outcome will be the pain NRS scores at 24 h postoperatively. These continuous data will be compared by independent two-tailed *t* tests if they are normally distributed or by Mann-Whitney *U* test if they are abnormally distributed. Similarly, secondary outcomes including pain NRS scores at 2, 4, 12, 48, and 72 h after craniotomy, sufentanil consumption with PCA device, PONV scores, WHOQOL-BREF, wound healing score, and POSAS scores at different time points and the duration of hospitalization will be compared by independent two-tailed *t* tests as normally distributed data or by Mann-Whitney *U* test as skewed data. In addition, the time to first button press or to first requirement of OC/PAPA will be compared by log-rank test and reported as hazard ratios (HRs) with 95% CI in Kaplan-Meier curves. Safety analyses will be compared with the incidence of AEs recorded in the safety data set using Chi-square test or Fisher’s exact test. The same statistical methods will be used for demographic characteristics and baseline information. We will judge a *P* value of less than 0.05 as significant for all tests.

Two interim analyses will be conducted for assessment of efficacy and safety after completion of the first 40 and 80 patients. The efficacy of the primary outcome and the incidence of AEs will be compared between two groups, and the study discontinuation threshold will be set at *P* < 0.01 using the alpha-sparing technique (O’Brien-Fleming) for benefit or harm.

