There are some limitations in our study. Firstly, this is a single-center study. However, ours is a large institution in Asia that specializes in neurosurgery and offers clinical, scientific, and teaching base of neurosurgery, which represents a great advantage in generalizability of our outcomes in this field. Secondly, neurosurgical patients have high levels of anxiety and depression, which are also possible risk factors for post-craniotomy pain [52]. However, due to the absence of a specialized assessor preoperatively, we will not able to control for these factors. Thirdly, we only select a single concentration of D-PAL as an infiltration adjuvant in this study. Future trials on dose-dependent effects of D-PAL should be warranted to determine the optimal dose. Fourthly, D-PAL is a non-transparent emulsion, and thus, surgeons and anesthesiologists will not be blinded in this study. Future studies should attempt to prepare the infiltration solution in non-transparent syringes. Fifthly, the sample size is not big enough to identify the risks of rare but important side effects, such as allergic reactions, systemic toxicity, infection, peptic ulcer, and changes in wound healing. A systemic review is the only way to establish these risks. Finally, an overview of case reports has determined that, in about half of cases with tissue atrophy or infection after local corticosteroid injection, the affected area returns to normal over a few months to years [53]. In this study, follow-up evaluations will be conducted within 3 months postoperatively, on account of the fact that we have selected a low concentration of dexamethasone for scalp infiltration, and the safety of local injection with dexamethasone and Diprospan has already been demonstrated in our previous work [6, 19]. However, it is suggested that the follow-up visit should be extended beyond 3 months in case of tissue atrophy or infection after local injection.

In conclusion, post-craniotomy pain is a common occurrence associated with poor outcomes. At present, there is no generally accepted opinion regarding the most suitable analgesic method. If our results reveal a significant decrease in postoperative analgesics with the addition of D-PAL emulsion in pre-incision infiltration, this trial will provide an effective alternative to optimize pain outcome for patients undergoing craniotomy.

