## Trial status

Not recruiting. Protocol (V3.2/2018-07-05). The recruitment will be expected to begin on October 1, 2022, and to be completed on May 1, 2023.

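### The interim rule can stop the trial for benefit on the 24 h pain score alone, with no link to the 3-month safety and recovery aims; under the plan's own assumptions this happens in about 62% of trials

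*Protocol article*

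**What the plan says.** Statistics: "Two interim analyses will be conducted for assessment of efficacy and safety after completion of the first 40 and 80 patients". At each look the primary outcome and the incidence of adverse events are compared between groups, and "the study discontinuation threshold will be set at" P < 0.01, in either direction, under an O'Brien-Fleming label. The primary outcome is NRS at 24 h. On the test, the section says "These continuous data will be compared by independent two-tailed *t* tests if they are normally distributed", with Mann-Whitney otherwise. It judges all tests at P < 0.05 and bases all analyses on patients who complete 3 months of follow-up. It does not say whether completion at an interim look means the 24 h score or the 3-month visit.

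Sample size: the plan will "attempt to detect a difference of 40% in pain NRS scores between groups at 24 h after craniotomy", from 2.0 ± 1.5 to 1.2 ± 0.9, with 65 per arm after 20% dropout.

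Objectives: the interventions' effects on patients' "safety and quality of recovery will also be compared". Secondary outcome and Safety assessment carry soft-tissue atrophy, wound healing, scar and quality of life to 3 months.

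Discussion: "the sample size is not big enough to identify the risks of rare but important side effects".

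Trial status: "The recruitment will be expected to begin on October 1, 2022, and to be completed on May 1, 2023".

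**The concern.** The rule lets one 24 h symptom score decide whether the trial goes on, although the trial also compares safety and recovery to 3 months. No minimum number of patients and no minimum safety follow-up is attached to a benefit stop.

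Two things are at stake. The first is the size of the pain effect. The Background says earlier positive results with dexamethasone may have had limited clinical significance because the absolute differences were small, so a good estimate of the difference is much of what this trial is for. Estimates from trials that stop on a boundary are too high on average. The second is the 3-month comparison of a local steroid mixture, which could end with fewer patients than planned. How many fewer depends on the undefined word.

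**Working it through.** **1. The plan's sample size.** Root-mean-square SD = √((1.5² + 0.9²)/2) = √1.53 = 1.237. With difference 0.8, two-sided 0.05 and 90% power, n = 2 × (1.960 + 1.282)² × 1.53 / 0.8² ≈ 50.2, so 51 per arm. The t test needs 52 (power 0.903). 52/0.8 = 65 per arm, 130 in total. The plan's figure reproduces.

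**2. Chance of crossing P < 0.01 at each look taken alone.** SE = √((1.5² + 0.9²)/n).
- 20 per arm: SE = √(3.06/20) = 0.391; Welch critical value 2.74; smallest difference that crosses = 2.74 × 0.391 ≈ 1.07 points (about 54% of the control mean, against the planned 40%); power 0.26.
- 40 per arm: SE = √(3.06/40) = 0.277; critical value 2.66; smallest difference ≈ 0.73; power 0.60.

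**3. Cumulative chance of an early benefit stop.** Simulated normal trials with a true difference of 0.80, P < 0.01 at both looks:

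| Scenario | Look 1 | Look 2 | Either look | Mean difference if stopped |
|---|---|---|---|---|
| Plan's SDs, 20 and 40 per arm | 26% | 36% | 62% | 1.06 |
| Plan's SDs, 20% dropout (16 and 32 per arm) | 19-20% | 30% | 50% | 1.15 |
| SD 1.5 in both arms, 20 and 40 per arm | 17% | 26% | 43% | 1.22 |

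In the first row the mean is 1.25 to 1.26 for a look-1 stop and 0.91 for a look-2 stop. Overall, 1.06/0.80 = 1.32, an overstatement of 32% given a stop. Averaged over all trials, stopped or not, the estimate is 0.88 (final 52 per arm) to 0.90 (final 65).

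**4. Same looks with real O'Brien-Fleming-type spending.** With 65 per arm as full information, the nominal two-sided levels are 0.0004, 0.012 and 0.045. Look-1 stops fall to about 5%, early stops overall stay at 62 to 63%, and the mean at stopping is 0.99. With 52 per arm as full information (0.0016, 0.025, 0.041), look-1 stops are about 10 to 11%, early stops overall 72 to 73%, and the mean 0.97.

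**5. Type I error.** A flat 0.01 at both looks followed by 0.05 at the end gives an overall two-sided error of about 0.06.

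**6. What a stop costs in safety patients.** Assume uniform accrual: 130/7 = 18.6 per month.
- *Completion means the 24 h score.* Look 1 falls at 40/18.6 ≈ month 2.2, when nobody has reached 3 months. Look 2 falls at 80/18.6 ≈ month 4.3, when about (4.3 − 3) × 18.6 ≈ 24 of 80 have. If accrual then stops, 20 or 40 per arm remain for safety.
- *Completion means 3-month follow-up.* Look 1 falls at about month 5.2 with about 96 enrolled (48 per arm). Look 2 falls at about month 7.3, after recruitment has ended, with all 130 enrolled.

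For a harm with no events in an arm, the two-sided exact 95% upper limit is 1 − 0.025^(1/n): 16.8% for 20, 8.8% for 40, 7.4% for 48 and 5.5% for 65.

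**The case against.** Stopping for efficacy under an independent DMC is an accepted design, and bias in the estimate given a stop is common to group-sequential trials. Averaged over all trials it is modest here: 0.88 to 0.90 against 0.80. The article may also leave the reason for the rule to the full protocol or a charter, so the absence of a stated reason is not held against it. All of this stands.

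A reader might infer that an early stop will cut the 3-month safety data to 20 or 40 per arm. The documents do not support that as a certainty. The DMC section reviews data at 30% and 60% of inclusions (39 and 78 patients), which sits close to 40 and 80 and favours the 24 h reading. But the Statistics section bases all analyses on patients completing 3 months, which favours the other. Stopping enrolment also does not end follow-up of those already treated.

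A reader might infer that an early stop is the most likely course of the trial. That holds at 62% but not at 43%, and Mann-Whitney on skewed, rounded scores lowers the figure further (about 54%, or 42% after dropout, for one assumed shape).

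A reader might also take the Discussion to say that 130 patients are too few for every harm of interest. It says so only of rare ones, which 65 per arm would not settle either.

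Finally, much of the alarm at look 1 comes from the flat 0.01. That is true of look 1 but not of early stopping overall, which stays near 62% under the boundary the plan names.

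**Conclusion.** The point holds in a limited form. The protocol fixes a benefit stop on 24 h NRS alone and does not reconcile it with its own 3-month aims. If the treatment works as planned, the stop is triggered in about 62% of trials, and in roughly 43% to 50% under a common SD of 1.5 or the planned dropout. The reported difference given a stop then averages 1.06 in place of 0.80.

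The loss of safety patients is conditional: substantial on the 24 h reading if accrual stops at once, and on the 3-month reading limited to about 17 per arm (65 − 48) at look 1 and none at look 2. On that second reading the look-2 stop spares no one, yet still spends an efficacy test. On neither reading does the rule gain much in a 7-month recruitment.

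These figures assume normal scores, equal numbers per arm at each look, a final test at 0.05 (or the spending levels shown) and uniform accrual. This is a cheap improvement to the design; the planned sample size itself is not in question.

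**What to change.** In the Statistics section, remove stopping for benefit on 24 h NRS. Keep the looks at 40 and 80 patients as safety reviews for the DMC, recruit all 130, and test 24 h NRS once, at two-sided 0.05. This removes the stopping bias and the excess type I error on either reading of completion, and keeps the full sample for the 3-month comparisons. It takes about one sentence of wording, in a trial listed as not yet recruiting. What is given up is the chance to end recruitment a few months early.

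If the sponsor prefers to keep a benefit stop, the protocol should define completion, state actual O'Brien-Fleming levels for each look and for the final test, and commit to 3-month follow-up of everyone already enrolled.

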## Data Monitoring Committee (DMC)

This trial will be monitored by an independent Data Monitoring Committee (DMC) composed of specialists in ethics, statistics, and methodology through regular interviews. The DMC will audit the assessment and collection of all data after 30%, 60%, and 100% of patient inclusions. DMC will have access to interim results. Any AE will be reported to both the DMC and the IRB for judgement. Although there are no anticipated problems that may be detrimental to the participants, serious life-threatening AEs leading to prolonged hospital stay or death will be reported and the study will be terminated immediately.

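### A constant P < 0.01 at both interim looks with an unreduced P < 0.05 at the end is not an O'Brien-Fleming design and puts overall two-sided type I error at about 5.7–5.9%

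*Protocol article*

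**What the plan says.** All references are to the protocol article.

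- **Statistics, looks:** "Two interim analyses will be conducted for assessment of efficacy and safety after completion of the first 40 and 80 patients". The primary outcome and adverse event incidence are compared between groups at each look.
- **Statistics, boundary:** "the study discontinuation threshold will be set at *P* < 0.01 using the alpha-sparing technique". O'Brien-Fleming is named in brackets, and the rule applies to benefit or harm. One value serves both looks.
- **Statistics, significance:** a P value "less than 0.05 as significant for all tests". No separate final level is given for the primary outcome.
- **Sample size:** PASS "is used for sample size calculation with *α* = 0.05, *β* = 0.1, and power = 90"%, with no mention of interim looks.
- **Data Monitoring Committee:** "The DMC will audit the assessment and collection of all data after 30%, 60%, and 100% of patient inclusions". The committee also has access to interim results.
- **Trial status:** "The recruitment will be expected to begin on October 1, 2022, and to be completed on May 1, 2023".

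**The concern.** An O'Brien-Fleming boundary is very strict at early looks, relaxes as information accumulates, and leaves a final level slightly below the nominal alpha. The stated rule does none of this: it is flat across the two looks and keeps the full 0.05 at the end. The named method and the stated numbers cannot both be followed.

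Two things are at stake. First, the chance of a false positive on the primary outcome exceeds the 5% used to size the trial. Second, a threshold of 0.01 at 20 patients per arm makes early stopping for benefit fairly likely. Stopping there yields an inflated estimate of the effect.

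**Working it through.** **Inputs.** From Sample size: means 2.0 and 1.2 (difference 0.8), SDs 1.5 and 0.9, alpha 0.05, power 90%, dropout 20%. From Statistics: a two-tailed primary test, looks at 40 and 80, P < 0.01 at each, P < 0.05 at the end. Alpha is taken as two-sided because the primary test is "compared by independent two-tailed *t* tests if they are normally distributed"; the sample size paragraph does not state sidedness.

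**1. The plan's own sample size.** The Welch t test with these means and SDs needs 52 per arm (power 90.3%). Allowing for dropout, 52/0.8 = 65 per arm, or 130 in total. The stated figure reproduces as a fixed design without looks. The evaluable number after 20% dropout is 130 × 0.8 = 104.

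**2. Information fractions.**
- Final N 130: 40/130 = 0.308, 80/130 = 0.615, 1.
- Final N 104: 40/104 = 0.385, 80/104 = 0.769, 1.

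**3. Overall type I error.** The three test statistics are multivariate normal with correlation √(tᵢ/tⱼ). The boundaries are |z| = 2.576, 2.576 and 1.960. The probability of first crossing at each look under the null is:

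| Final N | Look 1 | Look 2 | Final | Total |
|---|---|---|---|---|
| 130 | 0.0100 | 0.0077 | 0.0415 | 0.0592 |
| 104 | 0.0100 | 0.0077 | 0.0393 | 0.0570 |

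Simulation with 4 million replicates gives 0.0594 and 0.0568.

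**4. What O'Brien-Fleming would give** (nominal two-sided P, overall 0.05):

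| Version | N = 130 | N = 104 |
|---|---|---|
| Classical, C/√t | 0.0003 / 0.011 / 0.046 | 0.0011 / 0.021 / 0.043 |
| Lan-DeMets, total two-sided alpha in one function | 0.0004 / 0.012 / 0.045 | 0.0016 / 0.025 / 0.041 |
| Lan-DeMets, 0.025 per side | 0.0001 / 0.0085 / 0.047 | 0.0006 / 0.021 / 0.044 |

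At look 1, 0.01 is between 6 times (0.01/0.0016) and 100 times (0.01/0.0001) too lenient, depending on convention and final N. It comes close only at look 2 with 130 patients. Correcting the interim levels alone is not enough: the per-side Lan-DeMets levels followed by an unreduced 0.05 give an overall error of 5.3% (130) or 5.6% (104).

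**5. Final level if 0.01 is kept at both looks.** Solving for an overall 0.05 gives 0.040 (130) or 0.042 (104).

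**6. Early stopping under the planned effect, 20 per arm.**
- SE = √((1.5² + 0.9²)/20) = √(3.06/20) = 0.391.
- Expected z = 0.8/0.391 = 2.05.
- Chance of P < 0.01 in favour of D-PAL: 30% by the normal approximation, 26% by the Welch t test. At a threshold of 0.0004 it is 7% and 5%.
- Crossing requires an observed difference above 2.576 × 0.391 = 1.01, already more than the planned 0.8. The mean estimate given crossing is about 1.25.

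**7. Timing of the looks.** Uniform accrual is an assumption. The stated window is 212 days. Patient 80 is enrolled near day 80/130 × 212 = 130. With the 24 h outcome, the second look falls near 9 February 2023, well inside enrolment. If completion meant 3 months (about 91 days), it would fall near day 221, about 9 days after the planned close. The first look would then fall near day 65 + 91 = 156, with about 156/212 × 130 = 96 enrolled.

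**The case against.** The best defence is that this is a condensed article. It names a recognised alpha-control method, and the sentence on 0.05 is generic. The final primary-outcome level might be set in an analysis plan that is not shown, so the inflation would be possible rather than established. This has some force for the final level. It has none for the interim threshold, which is a stated number that does not fit the named method. As printed, the rule for all tests covers the primary outcome too.

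It is also fair that the excess is under one percentage point, and that the shortage of safety data at 20 per arm adds little: the Discussion already concedes that the full sample cannot identify rare harms.

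Two stronger readings are tempting and not supported.

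- **The second look comes too late to matter.** A reader might infer this because the Statistics section says all analyses include patients who complete 3 months. It needs that meaning of completion at the interim as well as uniform accrual, and the overshoot is only about 9 days. The efficacy comparison at each look is of a 24 h outcome. What stands is that completion is undefined.
- **The monitoring committee's schedule contradicts the looks.** Its 30% and 60% of inclusions are 39 and 78 patients, against 40 and 80. The text describes a data audit, which can coexist with the efficacy looks. Because the committee also sees interim results, the two should be aligned, but this is a clarification.

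**Conclusion.** The point holds. The stated boundary is not O'Brien-Fleming under any of the three versions checked. With 0.05 at the end, overall two-sided type I error is 5.9% at 130 patients or 5.7% at 104, an excess of 0.9 or 0.7 percentage points. The larger practical effect is a 26–30% chance, under the planned effect, of stopping for benefit at 20 per arm on an estimate of about 1.25 against a true 0.8.

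These figures assume that looks occur at exactly 40 and 80 analysed patients, that the boundary is applied as printed, and that the normal approximation holds for the error rate. They do not show that 130 is the wrong sample size, which reproduces; the fault lies in the monitoring rule. The rule should be settled before the first look, and the article lists the trial as not yet recruiting.

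**What to change.** Choose one of the following and state it in the Statistics section.

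- **(a)** Name a Lan-DeMets O'Brien-Fleming-type spending function and its convention, with levels recomputed at the actual information. At 40/80/130 these are 0.0004/0.012/0.045 if the total two-sided alpha is spent in one function, or 0.0001/0.0085/0.047 if 0.025 is spent per side. The convention must be named, because the first-look level differs fourfold between them.
- **(b)** Keep 0.01 at both looks, drop the O'Brien-Fleming label, and test the primary outcome at 0.040 at the end (0.042 if 104 are evaluable). This holds the overall error at 5% but leaves the lenient first look, so (a) is the better answer to early stopping.

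Under either option, replace the general 0.05 rule for the primary outcome with the chosen final level. Define completion of the first 40 and 80 patients as having the 24 h pain score, and tie the monitoring committee's schedule to the same trigger.

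The cost is wording and a little power. With 52 per arm, final-test Welch power falls from 90.3% to 89.3% at 0.0437, 88.7% at 0.0409 or 88.5% at 0.040. These are powers of the final test alone and ignore rejections at the interim looks. The sample size need not change.

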## Discussion

In this prospective, randomized controlled trial, we seek to determine whether pre-emptive scalp infiltration with the addition of D-PAL emulsion to ropivacaine would offer superior analgesic efficacy for post-craniotomy pain compared to ropivacaine alone. To the best of our knowledge, this is the first study to evaluate the effects of D-PAL emulsion in scalp infiltration for craniotomy. D-PAL emulsion, dexamethasone palmitate incorporated into lipid microspheres, has a stronger anti-inflammatory activity, as well as a longer duration of action and fewer side effects than free dexamethasone. The clinical utility of D-PAL emulsion has been reported to treat inflammatory diseases or pain diseases by intravenous administration or local infiltration [24, 25, 28, 29, 37]. In this study, we intend to choose the concentration of about 0.027% D-PAL (equivalent to 0.017% dexamethasone) for scalp infiltration, which seems to be the lowest possible concentration of dexamethasone for local use according to previous literatures [6, 37–39]; thus, it should be considered safe and help reduce the potential risks of local glucocorticoid, such as delayed wound healing and wound infection. It is true that systemic dexamethasone has become the standard pharmacological agent in the treatment of cerebral oedema associated with intracranial tumors [40]. Perioperative high-dose of dexamethasone in craniotomy has been reported to be associated with hyperglycemia, infection, peptic ulcer, and decreased incidence of PONV and pain [41]. All these may confound our findings. So the consumption of intravenous dexamethasone prescribed by the neurosurgeon should be calculated in the two groups.

Ropivacaine is the most widely used long-acting LAs for incisional infiltration [42]. In this study, we choose a widely used concentration of 0.5% ropivacaine for scalp infiltration in craniotomy [43, 44]. There are two main reasons for this. First, it is reported that scalp block using 0.5% ropivacaine has obtained preferable and prolonged postoperative analgesia compared to lower concentrations in craniotomy [45]. Second, ropivacaine is considered one of the safest LAs attributed to its lipophilicity, which leads to decreased toxicity in both cardiovascular and central nervous systems [46]. Moreover, the intradermal injection of 0.25-0.75% ropivacaine can induce peripheral vasoconstriction and decreases local blood flows at the injection [47]. It is reported that the peak plasm concentration of 0.5% ropivacaine occurs within 13 min after commencement of scalp infiltration without any signs of local anesthetic toxicity [40].

Mixtures of local anesthetics and steroids have been used in common practice. However, the safety of this mixture has not been considered carefully. Combination of non-particulate steroids with local anesthetics could form crystals in solution, which may be caused by alkalinization of steroids. The deposits of insoluble crystals could partly account for the depressed and atrophic skin at the site of injection [48]. However, it is recently reported that the mixture of D-PAL emulsion (with an almost neutral pH of 7.1) with ropivacaine produced no significant particulates under fluorescence microscopy [20], suggesting an optimal and safe combination for use in our protocol. As to the aseptic soft-tissue damage or infection after local injection, the occurrence and duration seem to be a function of local drug concentration [49]. In this study, we intend to choose the lowest possible concentration of dexamethasone for local use to achieve a safe regimen. To our knowledge, no serious local AEs have been reported concerning local infiltration with the mixture of D-PAL and ropivacaine [50]. However, the actual number of trials is limited, and therefore, additional studies regarding its potential safety and efficacy are needed in the future.

Craniotomy site may be a determinant for the incidence and intensity of post-craniotomy pain, which is partly explained by the anatomical location of peri-cranial muscles being damaged. Studies suggest that patients undergoing infratentorial procedures may have more pain than those submitted to a supratentorial approach [2]. Further studies indicate that supratentorial craniotomy involving temporal muscle incision is assumed to be more painful, while the procedure involving frontal muscle incision tends to induce the lowest pain [51]. Therefore, we specify the accurate location in this trial and restrict the surgical approach to be supratentorial.

There are some limitations in our study. Firstly, this is a single-center study. However, ours is a large institution in Asia that specializes in neurosurgery and offers clinical, scientific, and teaching base of neurosurgery, which represents a great advantage in generalizability of our outcomes in this field. Secondly, neurosurgical patients have high levels of anxiety and depression, which are also possible risk factors for post-craniotomy pain [52]. However, due to the absence of a specialized assessor preoperatively, we will not able to control for these factors. Thirdly, we only select a single concentration of D-PAL as an infiltration adjuvant in this study. Future trials on dose-dependent effects of D-PAL should be warranted to determine the optimal dose. Fourthly, D-PAL is a non-transparent emulsion, and thus, surgeons and anesthesiologists will not be blinded in this study. Future studies should attempt to prepare the infiltration solution in non-transparent syringes. Fifthly, the sample size is not big enough to identify the risks of rare but important side effects, such as allergic reactions, systemic toxicity, infection, peptic ulcer, and changes in wound healing. A systemic review is the only way to establish these risks. Finally, an overview of case reports has determined that, in about half of cases with tissue atrophy or infection after local corticosteroid injection, the affected area returns to normal over a few months to years [53]. In this study, follow-up evaluations will be conducted within 3 months postoperatively, on account of the fact that we have selected a low concentration of dexamethasone for scalp infiltration, and the safety of local injection with dexamethasone and Diprospan has already been demonstrated in our previous work [6, 19]. However, it is suggested that the follow-up visit should be extended beyond 3 months in case of tissue atrophy or infection after local injection.

In conclusion, post-craniotomy pain is a common occurrence associated with poor outcomes. At present, there is no generally accepted opinion regarding the most suitable analgesic method. If our results reveal a significant decrease in postoperative analgesics with the addition of D-PAL emulsion in pre-incision infiltration, this trial will provide an effective alternative to optimize pain outcome for patients undergoing craniotomy.

